### Statistical analysis

A statistical analysis plan will be written, including the following aspects: Descriptive analyses will be conducted to determine the study population characteristics and the differences in the primary and secondary outcomes between the study arms. The primary analyses will be based on the intention-to-treat principle. Both intervention arms will be compared with the control arm. Additionally, a more in-depth analysis for each outcome separately will be provided. A multiple-imputation procedure will be used to handle missing data. No interim analyses are carried out beforehand. The results of the analysis will be publicised to all relevant groups through publications and reports. Access to the protocol is possible upon reasonable request.

#### Primary outcomes

To test the effect of the intervention on the primary outcomes (health behaviours and health knowledge) at *t*2, both intervention arms will be compared to the control arm as adjusted for baseline values (*t*0) for the primary outcomes using multivariate regression analysis with random coefficients for district directorates. This method offers the option to control for potential baseline differences between study arms.

The health knowledge survey is structured as a knowledge test. All correct answers are added up at the end to give a score. The variables are dichotomous outcome variables (i.e., in agreement (yes) or disagreement (no/uncertain) with recommendations). For each variable, there are a number of multiple response categories for which women have to select one or more correct answers. The “correct answers” are based on the existing guidelines and recommendations of the federal government. For further details please see Oechsle et al.

The assessment of each category according to health behaviours is based on the fulfilment of applicable health behaviour recommendations (fulfilment of recommendations yes/no).”

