### Randomisation process

The 14 district directorates of AOK Baden-Wuerttemberg (Fig. 1), in Southwest Germany, are randomly assigned to one of the three study groups: the on-site intervention group, the online intervention group, or the control group. The initial randomisation process has been performed via computer generation and was carried out using a simple cluster-randomised design before the process of enrolment. The cluster randomisation will be conducted by an independent operator using the statistical program R (Version 1.3.5) with the randomizr package. The conduct of randomisation was concealed to the members of the study team. Similarly, the counsellors will be allocated according to their place of employment. Depending on where the insured people live, they will be assigned to the appropriate district directorate (e.g. if an insured person lives in the Ludwigsburg-Boeblingen area, she will be assigned to the Ludwigsburg-Boeblingen district directorate and the staff employed there). If an insured person is interested in the study, she will receive the intervention assigned to the responsible district directorate (e.g. insured person lives in the Ludwigsburg-Boeblingen area. The area has been assigned to intervention arm 1. The insured person is therefore automatically assigned to intervention arm 1). This means that the district directorates should be considered as randomised units.

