#### Other measures

All participants will be asked questions to determine their socio-demographic status. These include age, education, occupation, country of birth, parents’ countries of birth, and household income.

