### Sample size calculation

The power calculation was performed assuming a probability of successful participation by 50% of participants in the control group, and a perceived relevant improvement of the successful participation by 65% of participants in the intervention groups. These assumptions were based on the results of a cross-sectional study by Oechsle et al. [8] on the health knowledge of pregnant women regarding LRRFs, in which knowledge gaps and their health effects were identified, and on studies indicating the need for improvement in the health behaviours of pregnant women [5–7, 23]. We calculated the sample size for the primary outcome “health knowledge” because for this outcome, we could derive a valid effect size from previous studies.

Furthermore, sample size calculations were based on a power of (1 − *ß*) = 65% and a significance level of *α* = 5% (two-sided).

To account for the cluster structure, with participants nested within customer and service centres, a small intra-cluster correlation coefficient (ICC) of 0.01 was assumed. As there are 14 district directorates of AOK Baden-Wuerttemberg (arm one = 4, arm two = 5, arm three = 5), it is estimated that there would be approximately 36 participants per cluster (cluster = district directorate). Based on these assumptions and the perceived relevant difference of 50% in the control versus 65% in the intervention group, the sample size per study arm will be *n* = 168. This implies a total sample size of *n* = 504. A dropout rate of 20% is assumed; therefore, *n* = 638 participants must be enrolled in the study at time *t*0 to reach *n* = 504 for analysis.

The above calculations were performed using R (Version 1.3.5) and the sjstats package (Version 0.18.1).

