#### Other exploratory analysis

To further analyse which participants experienced behavioural and knowledge changes after the intervention, exploratory analysis will be performed. This analysis will investigate what factors influence behavioural and knowledge change, e.g. socioeconomic parameters (education, income, occupational status, and socioeconomic status), the number of previous pregnancies, the number of biological children, and previous counselling regarding LRRFs.

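### The primary model adjusts only for the t0 outcome value; a short pre-fixed list of individual-level t0 covariates would add a little precision and cover measured selection differences

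*Protocol article*

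**What the plan says.** The section Statistical analysis, Primary outcomes sets out the model. At t2 "both intervention arms will be compared to the control arm as adjusted for baseline values" of the primary outcomes, "using multivariate regression analysis with random coefficients for district directorates". It adds: "This method offers the option to control for potential baseline differences between study arms". No further covariate is named.

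Under Other measures, all participants are asked socio-demographic questions: "These include age, education, occupation, country of birth, parents’ countries of birth, and household income". Table 3 places these at t0. Their analytic use appears under Other exploratory analysis: "This analysis will investigate what factors influence behavioural and knowledge change, e.g. socioeconomic parameters". That section also lists the number of previous pregnancies, the number of biological children and previous lifestyle counselling.

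The Randomisation process section says that allocation of the 14 directorates "was carried out using a simple cluster-randomised design before the process of enrolment"; no stratification or balancing is mentioned. The Sample size calculation gives the split as "arm one = 4, arm two = 5, arm three = 5". Under Assignment of interventions, interested women are told during the telephone call which arm their directorate belongs to. The Statistical analysis section says that an analysis plan will be written and that missing data will be multiply imputed.

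**The concern.** With 4 or 5 directorates per arm and simple randomisation, the arms can differ noticeably in education, age or origin by chance alone. They can also differ for a reason that randomisation does not cover. The arm is known when a woman decides whether to take part, and a waiting list, a trip to a health centre and a video call may attract different women.

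The t0 outcome value removes whatever part of these differences is already visible at baseline. Any part that acts on t2 over and above t0 stays in the comparison. For chance differences the cost is precision, in a trial planned at 65% power. For selection differences it is possible distortion, and adjustment for measured factors can remove the measured part. The covariates are individual-level, so adding them uses essentially none of the few cluster-level degrees of freedom.

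**Working it through.** **Inputs from the protocol (Sample size calculation):** 50% v 65%, two-sided alpha 5%, power 65%, ICC 0.01, about 36 women per directorate, 168 per arm, directorates 4/5/5.

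**Assumed, because the documents do not give them:** the correlation between t0 and t2 (0, 0.5 or 0.7); the extra R² of the added covariates, as a share of the variance left after t0 (3%, 5% or 10%); the ICC of a covariate across directorates (0.01 or 0.05); and a residual correlation of 0.2 between covariate and outcome.

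**Step 1: reproduce the planned sample size.** Design effect = 1 + 35 × 0.01 = 1.35. With d = 0.15/0.5 = 0.30, a two-sample t-test at 65% power needs 123.2, so 124 per arm. 124 × 1.35 = 167.4, so 168. The stated figure reproduces. It contains no allowance for t0 adjustment.

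**Step 2: power gain from extra covariates.** Effective n per arm = 168/1.35 = 124.4. Power = Φ(0.30/√[(1 − ρ²)(1 − R²) × 2/124.4] − 1.96), where ρ is the t0–t2 correlation.

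| ρ | no extra covariates | R² 3% | R² 5% | R² 10% |
|---|---|---|---|---|
| 0 (no t0 adjustment) | 65.8% | 67.1% | 68.0% | 70.3% |
| 0.5 | 78.0% | 79.2% | 80.1% | 82.1% |
| 0.7 | 91.2% | 92.0% | 92.5% | 93.7% |

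The last two rows describe the planned model. At ρ = 0.5 the gain is about 1 to 4 points; at ρ = 0.7 it is about 1 to 2.5.

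A large-sample formula flatters a 14-cluster trial, so I repeated ρ = 0.5 with a t reference on 14 − 3 = 11 degrees of freedom and cluster-mean variance (1 − ρ²)(1 − R²)(0.01 + 0.99/36). For 5 v 5 directorates, power goes from 73.1% to 74.4%, 75.2% and 77.5%. For 4 v 5 it goes from 68.1% to 69.4%, 70.3% and 72.6%. The level is lower, but the gain is again about 1 to 4 points.

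**Step 3: how often would a covariate be unbalanced by chance?** For a 50% yes/no covariate, the SD of the between-arm difference is √[0.25 × (1 + 35 × ICC) × (1/(36k₁) + 1/(36k₂))].

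| Covariate ICC | Directorates | SD of difference | Chance of a gap above 10 points |
|---|---|---|---|
| 0.01 | 5 v 5 | 6.1 points | 10% |
| 0.01 | 4 v 5 | 6.5 points | 12% |
| 0.05 | 5 v 5 | 8.7 points | 25% |
| 0.05 | 4 v 5 | 9.3 points | 28% |

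**Step 4: how far would the estimate move?** Dividing these SDs by 0.5 gives 0.12 to 0.19 covariate SDs. At a residual correlation of 0.2, a one-SD imbalance shifts the effect by about 0.02 to 0.04 outcome SDs, against a planned 0.30. Chance imbalance is thus fairly frequent, but its effect on the estimate is small.

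The size of any selection difference cannot be derived from the documents.

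**The case against.** The strongest defence is that baseline-outcome adjustment with a directorate random term is a standard cluster-trial model, that t0 is usually the best single predictor, and that further covariates belong in the analysis plan still to be written. The first two points stand. The third stands only in part. The protocol does not leave the covariates open: it states which adjustment the primary analysis makes, and a plan that follows it would inherit the t0-only model.

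A reader might infer several stronger things, which the documents do not support:

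- **That the protocol expects these factors to drive change.** It says only that it will investigate which factors do. Factors that predict change are not automatically prognostic beyond t0.
- **That the word option permits choosing covariates after imbalances are seen.** The preceding sentence commits to t0 adjustment, and the remark most naturally describes what that adjustment makes possible.
- **That chance imbalance biases the result.** It does not over repeated randomisations, and the directorate term is meant to carry between-cluster variation into the standard error.
- **That the precision gain is large.** Strong assumptions can produce gains above ten power points, but they conflict with the planned ICC. A covariate with a coefficient of 0.35 outcome SDs and an ICC of 0.10 would alone contribute 0.35² × 0.10 = 0.012 of between-directorate variance, more than the whole planned 0.01.
- **That every candidate covariate is a t0 item.** Number of children, previous counselling and pregnancy status are not in the Other measures list, and no section dates their collection.

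**Conclusion.** The point holds as a modest improvement. The stated primary model is valid against chance imbalance and contradicts nothing in the protocol. It leaves unused individual-level information collected at t0, in a design with 14 simply randomised directorates and enrolment after the arm is known. The precision forgone is about 1 to 4 power points, for an assumed extra R² of 3–10% beyond t0. The more substantive reason to adjust is selection at the information call. The documents give no basis for sizing it, and adjustment would deal only with its measured part. Covariate strength, covariate clustering and the t0–t2 correlation are all assumptions.

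**What to change.** State the primary model for each outcome as arm + t0 outcome value + a short fixed list of individual-level t0 covariates + the directorate random effect. The list should contain age and education, with number of children, previous lifestyle counselling and pregnancy status added only if they are recorded at t0. Then:

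- fix the list before t2 data are opened by arm, and let this rule replace the sentence about an option to control baseline differences;
- include the covariates in the planned multiple imputation;
- for the yes/no behaviours, report adjusted risk differences, because adding covariates to a logistic model changes the meaning of the odds ratio;
- keep the t0-only model as a sensitivity analysis, and keep the exploratory section for the question of who changed.

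The cost is a few sentences in the protocol or analysis plan, a few more parameters and some covariate values to impute. No new participants or data are needed.

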#### Secondary outcomes

Client satisfaction with and the user-friendliness of the consultations will be analysed accordingly without, however, controlling for baseline values, as these questions are directly related to the intervention and will only be asked in the intervention groups at *t*1 and *t*2. Possible associations with potential improvements in health knowledge and health behaviours will also be analysed using multivariate regression analysis. In addition, an exploratory analysis to determine which materials influence the effectiveness of the intervention and whether these differ according to the form of counselling (on-site/online) will be conducted.

#### Other exploratory analysis

To further analyse which participants experienced behavioural and knowledge changes after the intervention, exploratory analysis will be performed. This analysis will investigate what factors influence behavioural and knowledge change, e.g. socioeconomic parameters (education, income, occupational status, and socioeconomic status), the number of previous pregnancies, the number of biological children, and previous counselling regarding LRRFs.

## Process evaluation

The process evaluation will aim to document the integrity of the planned procedures and processes, as well as to examine resources used during the counselling (interactive PDF shown via screen sharing, expert and explanatory videos, and information brochure). In addition, appraisals of future implementations of counselling interventions in health care settings will be collected.

### Study population

Initially, all participants in the intervention groups (*n* = 426) will be asked additional questions about the materials provided in the consultation.

Furthermore, interviews (*n* = 20–25) and two focus groups (*n* = 7 each) with trained study counsellors from AOK Baden-Wuerttemberg will be conducted to assess procedures and processes. All counsellors will be recruited via a shared e-mail distribution list created specifically for the purposes of the project.

### Data collection and measures

Quantitative data will be used for the evaluation of the materials. At survey times *t*1 and *t*2, the intervention groups will be asked additional questions regarding the comprehensibility and scope of the materials, the application of these materials by the participants, and the perceived relevance of the information. In addition, the extent to which used materials complemented the counselling will be assessed. For this, self-developed questionnaires were used.

To obtain more information on future implementation, the group of pregnant women and women of childbearing age will be analysed beyond the socio-demographic data. Furthermore, the counsellors’ understanding of their role as well as the location of the counselling service in the German health care landscape will be evaluated within the interviews. In addition, the question of whether the counselling is a complementary or a substitute service will be investigated. Focus groups with counsellors will be conducted to evaluate the procedures and processes of the intervention (scheduling appointment, technical equipment, and counselling procedure), and their potential improvement. The interviews and focus groups will take place online or on-site in August and September 2023 and last 45 min and 2.5 h, respectively. Interview guidelines will be developed for this purpose.

Verbal and written informed consent will be obtained from all focus group and individual interview participants. As this is a pseudonymous procedure, consent forms are required to be signed. Alongside the data from the quantitative survey, the qualitative data will be stored at Heidelberg University Hospital.

### Data analysis

Initially, the evaluation will include a descriptive analysis of the quantitative data regarding the materials, followed by an evaluation of customer satisfaction. Furthermore, exploratory analysis will be conducted to be able to establish possible correlations between process flow and satisfaction.

The focus groups will be video-taped and transcribed verbatim, as protocols [24]. The individual interviews will be audio-recorded and then also transcribed verbatim. All qualitative data will be subsequently analysed with the help of qualitative content analysis methods [25, 26].

## Discussion

An adequate basic knowledge of nutrition, physical activity, relaxation, stress management, and substance use during pregnancy is fundamental for beneficial personal health care. Particular emphasis is needed on supporting women to remain informed and aware of the connection between a healthy pregnancy and the negative effects of addictive substance use, such as with alcohol and tobacco.

Overall, this study proposes a contribution to the individual efforts of pregnant women towards preventing the negative impacts of unhealthy lifestyle choices and may reduce lifestyle-related pregnancy complications and outcomes. Furthermore, the positive effects of LRRF counselling during pregnancy have an impact not only on pregnant woman and their children but, also, in the best-case scenario, on the entire family by encouraging family members to make positive behavioural changes. In addition, this study will examine which factors positively influence the effectiveness of counselling. It is conceivable that, in a further step, the application of the developed intervention and materials in routine gynaecological and obstetric care will be evaluated. Counselling interventions, offered by health insurers, to raise awareness of the impact of LRRFs during pregnancy are a novel area of research. The scientific evaluation of the effect of such offers could contribute to the implementation of high-quality and cost-effective counselling services in the long term.

This study foresees some limitations. At present, participation is only possible for AOK Baden-Wuerttemberg-insured clients, representing 4.6 million persons in Baden-Wuerttemberg. In addition, it will be difficult to prevent survey participants from accessing published information, rather than reporting what they currently know. This concern applies to both the intervention and control groups and may be partially accounted for by recording the survey response times and taking them into account when interpreting the results. It is realistic to expect that a certain proportion of respondents will rate their health behaviours more highly on paper, than actually occurs in their lived experience, which is a natural reflection of the human need for social acceptance.

This study can help achieve national health goals and promote the effective contribution of evidence-based information and counselling to an improvement in public health. However, further research will be necessary to determine whether improving public health knowledge and potentially preventing pregnancy complications will have a positive impact on the economy and reduce individual and/or public health costs.

## Trial status

This is protocol version 4, date: 11 June 2024 Recruitment began on the 24th of April 2023 and will conclude at June 30, 2024. The Interviews were conducted in autumn/winter 2023 and the focus groups is planned for July 26, 2024.

## Data Availability

The dataset supporting the conclusions of this article is available from the authors but restrictions apply to the availability of these data, which were used under license from AOK Baden-Wuerttemberg (Germany) for the current study, and so are not publicly available. Data are, however, available from the authors upon reasonable request and with permission from AOK Baden-Wuerttemberg.

## Abbreviations

EHIS-PAQ: European Health Interview Survey-Physical Activity
ICC: Intra-cluster correlation coefficient
LRRFs: Lifestyle-related risk factors
NCDs: Non-communicable diseases
SCI: Stress and Coping Inventory
WHO: World Health Organization
